### Plans for collection, laboratory evaluation and storage of biological specimens for genetic or molecular analysis in this trial/future use {33}

This study does not involve the collection, storage, or laboratory evaluation of biological specimens for genetic or molecular analysis. All data collected will be observational, comprising non-invasive ocular measurements, demographic information, and behavioral risk factors related to myopia progression.

Accordingly:No biological samples (e.g., blood, saliva, or tissue) will be obtained from participants.No laboratory-based genetic or molecular testing is planned as part of the current study protocol or any ancillary study.All predictive analyses will rely solely on imaging (e.g., fundus photography) and structured clinical and environmental datasets.

## Statistical methods

### Statistical methods for primary and secondary outcomes {20a}

#### Primary outcome analysis

Objective: To quantify and predict myopia progression over time based on spherical equivalent refraction (SER) and axial length measurements.Approach:oDescriptive statistics (mean, standard deviation) will be used to report baseline characteristics.oLinear mixed-effects models will be applied to assess longitudinal changes in SER and axial length over follow-up periods, accounting for repeated measures and potential confounders (e.g., age, screen time, parental myopia).oTime-to-event analysis (e.g., Kaplan–Meier estimates) may be used to assess time to clinically significant myopic progression (e.g., ≥ –0.50 D/year), if applicable.

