### Objectives {7}

#### Primary objective

To develop and validate an artificial intelligence (AI)-based predictive model for assessing myopia progression among school-going children aged 6–18 years, based on demographic, environmental, and ocular health parameters.

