#### Secondary outcomes

AI Model Performance MetricsoMeasurement Variables: Accuracy, sensitivity, specificity, F1 score, AUROC (Area Under Receiver Operating Characteristic Curve)oAnalysis Metric: Model performance against test dataoMethod of Aggregation: Aggregated over cross-validation folds and independent test setsoTime Point: After complete data collection at each longitudinal stageoClinical Relevance: Demonstrates the utility of AI for triage and risk stratification without immediate clinical interventionIdentification of Dominant Risk FactorsoMeasurement Variables: Screen time, parental myopia, near work duration, outdoor activity, corneal curvature, axial length, etc.oAnalysis Metric: Feature importance scores and multivariate regression coefficientsoMethod of Aggregation: Ranked predictive power in final AI modeloTime Point: End of Phase 1 (cross-sectional analysis)oClinical Relevance: Supports public health planning and targeted interventionsMobile Application Usability and AccuracyoMeasurement Variables: Accuracy of app-based predictions compared to clinical diagnosesoAnalysis Metric: Positive predictive value, user-reported ease-of-use scoresoMethod of Aggregation: Mean values and usability ratings (Likert scale)oTime Point: Pilot deployment at 18 monthsoClinical Relevance: Determines the viability of a scalable school-level screening tool

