#### Model sensitivity and robustness checks

Internal cross-validation (e.g., k-fold) and bootstrapping will be performed.Sensitivity analysis will test the impact of varying thresholds for clinically significant myopia progression (e.g., ≥ –0.50 D/year vs. ≥ –1.00 D/year).Sub-models excluding outliers or high-leverage data points will be analyzed to assess stability.

These additional analyses will support the rigor, reproducibility, and real-world applicability of the developed AI model.

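### The primary outcome is a group mean change although the primary objective is predictive accuracy, and the progression thresholds are written with the inequality reversed

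*Protocol article*

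**What the plan says.** All references are to the protocol article.

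- **Primary objective:** "To develop and validate an artificial intelligence (AI)-based predictive model for assessing myopia progression among school-going children aged 6–18 years". The Hypothesis adds that the prediction will be accurate.
- **Outcomes {12}, Primary outcome:** the variable is named as a risk. It is measured as change in SER and axial length and summarised as a mean change from baseline at each six-monthly visit, within strata of age, location and baseline refractive status. A closing sentence says that AUROC, sensitivity and specificity will be assessed against this change.
- **Outcomes {12}, Secondary outcomes:** the first entry is model performance, listed as "Accuracy, sensitivity, specificity, F1 score, AUROC (Area Under Receiver Operating Characteristic Curve".
- **Primary outcome analysis {20a}:** the aim is "To quantify and predict myopia progression over time based on spherical equivalent refraction (SER) and axial length measurements". The method is a linear mixed-effects model of SER and axial length. A time-to-event analysis is optional, for "time to clinically significant myopic progression (e.g., ≥ –0.50 D/year".
- **Model sensitivity and robustness checks {20b}:** the threshold is to be varied, "e.g., ≥ –0.50 D/year vs. ≥ –1.00 D/year".
- **Participant timeline {13}:** baseline is in months 2–9, and follow-up visits are at months 18, 24, 30 and 36.

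**The concern.** Two faults bear on the same quantity.

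First, the outcome ranked primary is not the one that tests the hypothesis. A mean change describes how the cohort's eyes develop. It would come out the same whether the model predicted well, badly or not at all. The measures that do bear on the hypothesis sit in the secondary tier. They are tied to two continuous variables, whereas AUROC, sensitivity and specificity require each child to be classed as event or non-event.

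Second, the thresholds that could supply the event point the wrong way. Myopic progression makes SER more negative, so a change at or above –0.50 D/year is slow progression, no change, or a shift towards hyperopia. Model development belongs to a data-science team at a different institution from the clinical team. A rule that a clinician would silently correct could there be coded as printed.

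**Working it through.** **1. Objective against outcome**

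| Element | What it concerns | Contains a model prediction? |
|---|---|---|
| Primary objective, Hypothesis | Accuracy of predicted progression | Yes |
| Primary outcome | Stratified mean change in SER and axial length | No |
| Primary analysis | Mixed models of that change | None stated |
| First secondary outcome | Accuracy, sensitivity, specificity, F1, AUROC | Yes |

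The sentence closing the primary outcome shows that a link is intended. It does not move the metrics into the primary tier, and it names a continuous reference rather than an event. The Phase 2 sample-size text claims more than 80% power for AUC, sensitivity and specificity, so the sponsor already treats these as central.

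**2. The inequality on signed annual SER change**

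| Change (D/year) | ≥ –0.50 (as written) | ≤ –0.50 | ≥ –1.00 (as written) | ≤ –1.00 |
|---|---|---|---|---|
| +0.25 | event | no | event | no |
| 0 | event | no | event | no |
| –0.25 | event | no | event | no |
| –0.50 | event | event | event | no |
| –0.75 | no | event | event | no |
| –1.00 | no | event | event | event |
| –1.25 | no | event | no | event |

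As written, every child who meets ≥ –0.50 also meets ≥ –1.00. The sensitivity analysis would therefore loosen the definition where a stricter one was presumably wanted.

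**3. Size of the mislabelling**

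The article gives no distribution of annual change, so a normal distribution with assumed mean m and SD s is used. The share as written is 1 – Φ((–0.50 – m)/s). The share with the sign corrected is Φ((–0.50 – m)/s).

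- m = –0.30, s = 0.30: z = –0.667, giving 75% as written and 25% corrected. At –1.00 the shares are 99% and 1%.
- m = –0.30, s = 0.50: z = –0.40, giving 66% and 34%. At –1.00 they are 92% and 8%.
- Over m from –0.10 to –0.70 and s from 0.30 to 0.50, the –0.50 rule labels 25–91% as written and 9–75% corrected.

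Apart from children at exactly –0.50, the two labels are complements. A score trained for the intended event but scored on the inverted label would show 1 – AUROC. If it is both trained and scored on the inverted label, AUROC is unchanged. Sensitivity and specificity then refer to the opposite class, and the children flagged are those who are not progressing.

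**4. Time base for a rate per year**

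- Baseline to T1: 18 – 9 = 9 months to 18 – 2 = 16 months, not 6.
- Baseline to T4: 36 – 9 = 27 months to 36 – 2 = 34 months, not 24.
- A rate of –0.50 D/year then corresponds at T4 to –0.50 × 27/12 = –1.13 D up to –0.50 × 34/12 = –1.42 D. Over a nominal 24 months it would be –1.00 D.
- Conversely, a total change of –1.00 D divided by a nominal two years reads as –0.50 D/year. On actual dates it is –1.00 × 12/27 = –0.44 to –1.00 × 12/34 = –0.35 D/year.

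The rate must therefore be computed on actual dates.

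**The case against.** The strongest reply is that this concerns ranking and notation, not substance. The study calls itself exploratory, and no alpha is allocated between tiers. The performance metrics, cross-validation, independent test sets and bootstrapping are planned and will be reported whatever their rank. The primary analysis states prediction as part of its aim. The thresholds are given as examples, the time-to-event analysis is optional, and the words around the threshold make the intended direction plain. An ophthalmologist panel verifies progression status and settles borderline cases. A separate statistical analysis plan, not seen here, may fix the label and the horizon.

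Much of this stands, and it limits the severity. It does not remove the point. The outcome hierarchy and the reversed sign are stated in the article itself, so they are not details left to another document. The sign fault appears in both places where a threshold is given.

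Three stronger readings are tempting but not supported:

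- A reader might infer that the study cannot answer its primary objective. It can, because the metrics are planned and linked to SER and axial-length change. They are ranked below an outcome that does not bear on the objective.
- A reader might infer that –0.50 D/year is the only threshold in the plan. The robustness checks add –1.00 D/year.
- A reader might infer that annualising single six-month changes would turn measurement noise into lasting false events in many stable children. No section says that the rate is computed between consecutive visits. The primary outcome defines change from baseline, the first interval is 9–16 months, and no measurement SD is given. Any such percentage would rest on the reader's own assumptions, and it would also have to allow for the adjudication panel and the duplicate readings.

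**Conclusion.** The point holds and should be acted on. The primary outcome and its analysis measure average progression, whereas the objective and hypothesis concern predictive accuracy. The measures that would address these are secondary and are set against a continuous change. This follows from the text alone.

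The thresholds in the primary analysis and in the robustness checks are reversed as written. Taken literally, they select stable and slow-changing children and swap the strict and loose definitions. The intended meaning is probably a myopic shift of at least the stated size, so this is a notation error that does harm only if it is coded literally. How many children would then be mislabelled depends on the assumed distribution in the working. The direction of the error does not.

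**What to change.** - **Outcome hierarchy.** Make one discrimination measure the primary outcome, for example the AUROC of the final model for a single binary progression event at a fixed horizon visit. Keep mean SER and axial-length change, with the mixed models, as descriptive outcomes.
- **Sign.** Keep the sponsor's own thresholds but write them unambiguously: SER change ≤ –0.50 D/year, with ≤ –1.00 D/year as the sensitivity definition. Whether these are the right clinical cut-offs is for the investigators.
- **Time base.** Compute the rate as (SER at the horizon visit – SER at baseline) divided by the actual elapsed time in years.
- **Consistency.** Reconcile the primary and secondary outcomes, the primary and secondary outcome analyses, and the robustness checks. State whether axial length plays any part in the event.

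The cost is a protocol amendment with ethics committee approval, a registry update and one label definition. No extra visits, measurements or children are needed. It is best done before any follow-up label is coded, and the first follow-up visit is at month 18.

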#### Secondary outcome analysis

AI Model Performance Metrics:oAlgorithms including linear regression, support vector machines, XGBoost, random forests, and deep learning models (e.g., CNNs) will be trained and validated.oEvaluation metrics: Accuracy, sensitivity, specificity, F1 score, AUROC, AUPRC (as appropriate for classification tasks).oCross-validation techniques (e.g., 5-fold or 10-fold) will be used to ensure robustness and prevent overfitting.Identification of Dominant Risk Factors:oMultivariable logistic regression and feature importance analysis (e.g., SHAP values for tree-based models) will identify significant predictors of myopia progression.oInteraction effects (e.g., between screen time and outdoor activity) will be explored.Mobile Application Validation:oAgreement between app-predicted and clinician-confirmed cases will be assessed using Cohen’s kappa coefficient.oUsability scores from field users will be analyzed using descriptive statistics and Likert scale summaries.

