#### Secondary objectives

To systematically collect and analyse cross-sectional and longitudinal data on myopia-related risk factors in children from diverse socio-economic backgrounds in urban and rural areas of the Bhopal division.To identify and rank key predictors (e.g., axial length, screen time, parental myopia) contributing to myopia progression using machine learning algorithms.To design and deploy a mobile application embedded with the AI model to facilitate field-level risk prediction and early screening without the need for specialist intervention.To conduct awareness programs aimed at the prevention and early intervention for myopia progression in school children. 

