#### Phase 2: longitudinal cohort

A subset of 10% (approx. 500 children) will be selected from Phase 1 using AI-based parameter selection and stratified sampling (equal representation of myopic and non-myopic participants). This sample size is adequate for:Detecting meaningful differences in myopia progression rates (in diopters and axial length)Training and validating AI models using longitudinal data with multiple follow-upsEnsuring sufficient statistical power (> 80%) for machine learning model performance metrics such as AUC, sensitivity, and specificity

Sample size assumptions were determined in consultation with biostatisticians and are justified based on the objectives of developing and validating a predictive AI tool, rather than testing clinical efficacy of an intervention.

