#### Subgroup analyses

The following predefined subgroups will be analyzed to assess variability in myopia progression and predictive model performance:Age groups: 6–10 years, 11–14 years, 15–18 yearsGeographic location: Urban vs. rural participantsGender: Male vs. femaleBaseline myopia status: Myopic vs. non-myopic at enrolment. Parental myopia: Present vs. absent

Subgroup analyses will involve stratified modeling and comparative evaluation of outcome trends using interaction terms within regression models.

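### Importance scores are said to identify 'significant' predictors and alone set the rank of risk factors, yet they have no null; with a tree-based final model, yes/no factors also tend to be under-ranked

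*Protocol article*

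**What the plan says.** The secondary objective is "To identify and rank key predictors (e.g., axial length, screen time, parental myopia) contributing to myopia progression using machine learning algorithms". Under Outcomes {12}, Secondary outcomes, the candidates for dominant risk factor are "Screen time, parental myopia, near work duration, outdoor activity, corneal curvature, axial length, etc". The metric there is importance scores together with regression coefficients, but the aggregation is the rank of each factor by predictive power within the final AI model. The time point is "End of Phase 1 (cross-sectional analysis").

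The Secondary outcome analysis section opens the relevant sentence with multivariable logistic regression and continues: "feature importance analysis (e.g., SHAP values for tree-based models) will identify significant predictors of myopia progression". It does not say which method settles the matter if they differ. Under Model sensitivity and robustness checks, "Internal cross-validation (e.g., k-fold) and bootstrapping will be performed"; these are listed as checks on the model and are not linked to the ranking. The section Reference to statistical analysis plan (SAP) says that model selection criteria, tuning parameters and subgroup strategies are in a separate document.

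**The concern.** A mean absolute SHAP value or an impurity score describes how much a fitted model uses a variable. It cannot be negative and has no reference distribution, so no value of it is evidence against no association. Calling predictors significant on that basis is a wrong inferential statement, even with a valid method named beside it.

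Tree-based scores are also uneven across variable types. Among 500 distinct values a continuous variable offers up to 499 cut-points; a yes/no variable offers one. Noise in axial length or screen time therefore has more chances to be used than noise in parental myopia.

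The ranking is meant to guide public-health planning. A reader could take a noise variable for a dominant factor, or discount a real yes/no factor because it stands low in the list.

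**Working it through.** The plan gives no figure on this point to reproduce, so the check is by reasoning and simulation.

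**Inputs from the Protocol article**
- Parental myopia is treated as yes/no: "Parental myopia: Present vs. absent" (Subgroup analyses). Its coding as a predictor is not stated.
- Progression is observed only in the follow-up cohort: "A subset of 10% (approx. 500 children) will be selected from Phase 1" (Phase 2: longitudinal cohort).
- Phase 1 has about 5,000 children (Sample size {14}), where a 3.4% myopia rate is also given. That rate serves here as a rare-event case.

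**Assumptions, not in the document**
- Design A: 5 continuous and 3 binary predictors, 25% events, depth-1 boosted trees, parental myopia the only true predictor when there is one.
- Design B: 6 continuous, one five-level and 3 binary predictors, all independent; 30% progression; 30% parental myopia; XGBoost with 100 rounds at depth 3 or 1; also random-forest impurity importance.

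**Step 1: no null.** The score for variable j is the mean over children of |SHAP value|. It is above zero whenever the model splits on j, whether or not j matters. In design B with no true predictor (n = 500), all 10 scores were non-zero in 92% of runs at depth 3. At depth 1 this was so in only 1%, but the variables used were still ordered.

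**Step 2: evenness when nothing predicts**

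| Setting | Even-handed share | A binary factor first | Parental myopia in bottom three |
|---|---|---|---|
| A, depth 1, n = 500 | 3/8 = 37.5% | 4.3-7.0% | 82-89% |
| B, depth 3, n = 500 | 3/10 = 30% | 0.5% | 83.5% |
| B, depth 1, n = 500 | 30% | 4.5% | 81% |
| B, random-forest impurity, n = 500 | 30% | not recorded | 100% |
| B, depth 3, n = 5,000 (40 runs) | 30% | 0% | 80% |

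On the design A data, ranking by logistic p-value put a binary factor first in about 37-41% of runs. In design B the mean rank of parental myopia by logistic |z| was 5.4, against (1 + 10)/2 = 5.5 expected.

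**Step 3: a real yes/no factor, n = 500**

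| Design A, parental myopia ranked first | SHAP | Logistic test |
|---|---|---|
| Odds ratio 1.5 | 14.7-27% | 53.7-59% |
| Odds ratio 2.0 | 52.7-78% | 87.0-92.7% |

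The ranges span 50 to 300 boosting rounds and repeated simulations. With 300 runs, the simulation standard error near 20% is √(0.2 × 0.8/300) = 2.3 percentage points.

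In design B, parental myopia had odds ratio 2.0 and screen time the same log-odds per standard deviation: 0.693 × √(0.3 × 0.7) = 0.318.
- SHAP placed parental myopia below at least one pure-noise continuous factor in 71% of runs at depth 3 and 37% at depth 1.
- SHAP placed it below screen time in 82% and 64%. Logistic |z| did so in 51.5% and 51%, which is even.
- Random-forest impurity placed it below all five noise factors in 100%.

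**Step 4: a real yes/no factor, n = 5,000 (design A, depth 1)**

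| Events | Number of events | First by SHAP, OR 1.5 | First by SHAP, OR 2.0 |
|---|---|---|---|
| 25% | 5,000 × 0.25 = 1,250 | 99-100% | 100% |
| 10% | 5,000 × 0.10 = 500 | 91% | 100% |
| 3.4% | 5,000 × 0.034 = 170 | 41% | 90% |

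A repeat gave 87-100% where the event was not rare and 45% at 3.4% events with odds ratio 1.5. The number of events appears to matter most: 500 children at 25% give 125 events, close to the 170 of the rare-event case. The uneven ordering of pure-noise factors stayed at 5,000, with parental myopia in the bottom three in 80-88% of runs.

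**Step 5: regression also needs care.** In design B with no true predictor (n = 500), parental myopia reached p < 0.05 in 5.5% of runs, as it should. But at least one of the ten factors did so in 44.5%; the independence formula gives 1 − 0.95^10 = 40.1%.

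**The case against.** A reader might infer from the quoted words that significance is read from SHAP alone. The document does not support that: the same sentence names multivariable logistic regression, the outcome definition lists regression coefficients, and Adjusted analyses plans covariate-adjusted models. A valid test is already in the plan.

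A reader might also infer that yes/no factors will be under-ranked in any case. That does not follow. The final model is the best performer among linear regression, support vector machines, XGBoost, random forests and deep learning, so it may not be tree-based, and the effect varies with tree depth, which is left to the SAP. Nor can the results for 500 children be carried over to Phase 1, the stated time point, where step 4 shows a real factor is mostly ranked correctly.

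That some factor always comes first is true of any ranking, including one by p-value, and is not itself a defect. The study calls itself exploratory, this is a secondary outcome, and details such as permutation nulls are commonly left to an SAP.

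All of this narrows the point. What remains is in the text itself: importance scores are credited with finding significant predictors, no rule says which method decides, and the rank is defined by the final AI model alone. An SAP could supply a null or a tie-break, but the outcome and analysis wording would still need correcting. The follow-up cohort is also the only place where progression can be ranked, so the results at 500 remain relevant.

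**Conclusion.** The point holds in limited form. The absence of a null applies to importance scores from any model and needs no simulation. The push against yes/no factors is conditional on a tree-based final model and on its tuning.

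In the cohort of about 500, under the assumed 25% events and odds ratio 1.5, a real parental myopia effect came first in about 15-27% of runs by SHAP against about 54-59% by logistic test. At odds ratio 2.0 the gap was about 53-78% against 87-93%. At about 5,000 children the misplacement of a real factor largely disappears unless the event is rare, though noise factors are still ordered unevenly.

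Two limits apply. Outcomes were generated from a logistic model, which favours the logistic test. No result with a real factor at 5,000 is available for design B, that is, for depth-3 XGBoost or random-forest impurity. The primary outcome is not affected. The wording should be corrected before the risk-factor analysis is run.

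**What to change.** In Secondary outcomes and Secondary outcome analysis, call a predictor significant only on the basis of the multivariable regression coefficients, with 95% confidence intervals and multiplicity control across the candidate list (for example, a false-discovery-rate procedure). Present SHAP and other importance scores as a description of the fitted model.

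Where a ranking is shown:
- compute it on held-out folds;
- give bootstrap intervals for each factor's rank, using the bootstrapping already planned;
- compare each score with its own null, obtained by refitting after permuting the outcome;
- do not call a factor dominant if its score lies inside that null.

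The cost is some rewording and the computing time for the refits. Fewer factors will be called significant, and many ranks are likely to have wide intervals.
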